## Abstract

**Background:**

Globally, eye care provision is currently insufficient to meet the requirement for eye care services. Lack of access and awareness are key barriers to specialist services; in addition, specialist services are over-utilised by people with conditions that could be managed in the community or primary care. In combination, these lead to a large unmet need for eye health provision.

We have developed a validated smartphone-based screening algorithm (Peek Community Screening App). The application (App) is part of the Peek Community Eye Health system (Peek CEH) that enables Community Volunteers (CV) to make referral decisions about patients with eye problems. It generates referrals, automated short messages service (SMS) notifications to patients or guardians and has a program dashboard for visualising service delivery.

We hypothesise that a greater proportion of people with eye problems will be identified using the Peek CEH system and that there will be increased uptake of referrals, compared to those identified and referred using the current community screening approaches.

**Study design:**

A single masked, cluster randomised controlled trial design will be used. The unit of randomisation will be the ‘community unit’, defined as a dispensary or health centre with its catchment population. The community units will be allocated to receive either the intervention (Peek CEH system) or the current care (periodic health centre-based outreach clinics with onward referral for further treatment). In both arms, a triage clinic will be held at the link health facility four weeks from sensitisation, where attendance will be ascertained. During triage, participants will be assessed and treated and, if necessary, referred onwards to Kitale Eye Unit.

**Discussion:**

We aim to evaluate a M-health system (Peek CEH) geared towards reducing avoidable blindness through early identification and improved adherence to referral for those with eye problems and reducing demand at secondary care for conditions that can be managed effectively at primary care level.

**Trial registration:**

The Pan African Clinical Trials Registry (PACTR), 201807329096632. Registered on 8 June 2018.

**Electronic supplementary material:**

The online version of this article (10.1186/s13063-019-3615-x) contains supplementary material, which is available to authorized users.

## Background

Globally, it is estimated that 253 million people have visual impairment (VI; visual acuity in the better eye < 6/18), 36 million of whom are blind (visual acuity in the better eye < 3/60) [1]. About 80% of the impairment is avoidable [2]. Approximately 90% of those who are living with VI are in low- and middle-income countries [3]. Although the prevalence of moderate or severe vision impairment in adults aged ≥ 50 years is higher in South and Southeast Asia, North Africa, and the Middle East [4], sub-Saharan Africa (SSA) has the greatest gap between need (blindness VI) and available eye services [5]. In Kenya, the prevalence of blindness is high; it is in the range of 0.6–2.0%, depending on the region [6–10]. There are only 115 ophthalmologists for a population of 49 million. Moreover, their distribution is very uneven, in the range of 0–17 per 1 million population across the various counties [11].

The causes of blindness vary according to regions and countries [12–15]. Globally, the leading causes of VI are uncorrected refractive error and cataract, while cataract and glaucoma are the leading causes of blindness [2, 16]. Other causes of blindness include diabetes, macular degeneration, and other posterior eye diseases [7, 10, 17].

The reasons for a high burden of VI include poverty and a lack of access to eye services [18]. Patient factors such as lack of awareness, fear of treatment outcomes, increasing age, female gender, and presence of diabetes increase the risk of blindness [10, 19]. Health system-related factors include low numbers of eye workers, variable productivity, high indirect and direct costs, and the mal-distribution of the work force, which currently favours major urban areas [20–23]. In addition, there are ‘provider’ factors, such as poor-quality services arising from a shortage of trained staff and infrastructure [19, 24]. There is a large disparity between the need for eye services and availability of eye care workers [5].

To improve access to eye health services, especially in rural areas, outreach programs designed to promote access to eye services by communities in remote regions have been used [22, 25]. They provide short-term access to eye services for patients; however, the long-term goal is to integrate eye services into primary healthcare (PHC) as a continuum of health service provision [26, 27]. Redistribution of tasks among health workforce teams, to improve efficiency among available human resources, have also been used with variable success [9, 28]. Effective task shifting with clear referral criteria and management plans has been successfully delivered through algorithms such as the Integrated Management of Childhood Illness (IMCI) at primary level [29, 30]. In eye care, decision trees and algorithms have been developed, mostly outside Africa, and focused on identifying the diagnosis and treatment at a secondary level [31–33]. The World Health Organization (WHO) recently developed similar algorithms and training manual for use at the PHC facilities in Africa [34]. To our knowledge, there are no digital algorithms to identify and refer people from communities.

### Rationale

There is a clear need for improved access to eye health services for populations in many regions of the world. Availability of mobile phone technology and its usage in healthcare, including eye care, is increasing rapidly [35, 36]. One such example is Peek acuity, which has developed applications (Apps) for measuring visual acuity [37]. One study in Kenya showed that the Peek Visual Acuity App was a repeatable, accurate and reliable measure of visual acuity in adults [38]. This App was found to be acceptable to patients, care givers and stakeholders [39]. Another study among school-going children compared the performance of teachers using the Peek Acuity App to assess children’s vision to a clinician assessing the same children using as standard backlit EDTRS LogMAR visual acuity test chart found a sensitivity of 77% (95% confidence interval [CI] = 64.8–86.5) and specificity of 91% (95% CI = 89.3–92.1) [40]. We initially developed and validated the ‘Peek community screening App’ that allows referral decisions to be made precisely and reliably across all ages for the trial. Results from the validation of this App showed that community volunteers (CV) could accurately make referral decisions (manuscript in preparation).

A recent systematic review showed that mobile health (m-Health) interventions that support communication between healthcare providers and patients through short messaging service (SMS) appointment reminders are beneficial [41]. Similarly, outreach service provision in India incorporated the electronic transfer of health-related data from outreach clinics to base hospitals with some success [42]. This provides an opportunity for a combined outreach model, which incorporates triage and referrals aided by mobile technology.

We recently conducted a cluster randomised controlled trial in primary schools in Kenya using the Peek School Eye Health system. The system uses the Peek Acuity App to detect VI in school children. For those that then screen positive and who require further assessment or follow-up, it generates automated text messages to parents/guardians and contact teachers, as well as real-time notifications to hospital services. We found that teachers could reliably screen for VI. Uptake of referrals to eye care providers was substantially higher in the Peek intervention arm of this school trial [40]. This trial provided evidence that m-Health solutions could be used to improve access to eye health services.

In this new trial, the Peek Community Eye Health (Peek CEH) system will be compared to the current standard approach of periodic health centre-based outreach clinics. The system uses the ‘Peek Community Screening App’, which is a smartphone-guided algorithm for supporting ‘Peek Users’ to identify and refer people with visual impairment and other eye problems in the community. Peek Users are CVs who are trained specifically in how to use Peek. They travel to multiple communities to perform their duties. During community outreach, they work with the local CVs to identify and refer patients needing ophthalmic attention. Although treatment will be provided at no cost, it is assumed that: (1) all patients trust the health system; (2) eye health workers have the capacity and able to manage all conditions; and (3) relevant treatment modalities will be available.

### Objectives

The objective of this cluster randomised trial is to test the hypothesis that the Peek CEH system can increase access to eye services through: (1) increased identification of people with impaired vision and eye problems in the community; (2) increased uptake of a referral within four weeks by patients with identified an eye problem; and (3) more appropriate utilisation of primary and secondary care services at each health system level.

## Methodology

This protocol is structured in accordance with the Standard Protocol Items: Recommendations for Intervention Trials (SPIRIT) 2013 Checklist [43] (see Additional file 1).

### Trial design and overview

This trial is a single-masked, parallel-group, cluster randomised controlled trial. Thirty-six community units with their health facilities (dispensary or health centres) will be randomly selected to receive either the intervention (community screening using the Peek screening system) or the current standard of care (periodic health centre-based outreach clinics). The health workers involved in the study will be trained to ensure standardised screening. Participants who provide consent will be enrolled to the arm to which their cluster is randomised.

In the Peek arm, all households in the cluster will be visited in turn. Consenting individuals will have their visual acuity tested using the Peek visual acuity screening application on a smartphone. All participants with reduced visual acuity or reporting another eye problem will be referred to the linked PHC for assessment and management. Those requiring treatment not available from the PHC facility will be referred onwards to Kitale Eye Unit (KEU). In the control arm, communities will be notified about the periodic eye health outreach clinic that will be held in the local health centre. People attending this service will be assessed and, if necessary, referred onwards to KEU.

The participants will be followed up for eight weeks after referral from the community. The primary outcome will be the number of people per 10,000 population (rate) attending triage at a local health facility (PHC) with any confirmed eye conditions (true-positive cases determined at triage by hospital outreach team) following a referral or by self-referral within four weeks from the time of sensitisation. The secondary outcome will be the proportion of people referred from the PHC triage attending their referrals at KEU within four weeks of being referred. A participant (standard or Peek) who attends the hospital appointment within four weeks will be considered an ‘attender’ while anyone who is referred but does not attend within the same time is a ‘non-attender’.

### Participant timeline and study flow chart

The study flow chart and participant timeline are presented in Fig. 1 and Table 1, respectively.

**Fig. 1 Fig1:**
[figure not shown]
Trial design outline: randomisation, interventions and flow of participants

**Table 1 Tab1:** Project timeline

	Study period											
	Enrolment		Allocation	Post allocation								Close-out
Week	– 2	− 1	0	1	2	3	4	5	6	7	8	9
Preparation												
Training of field workers	X	X										
Approvals: Trans Nzoia health department and head of health facilities	X											
Community enumeration and obtaining consent	X	X										
Allocation of community units			X									
Interventions												
Community sensitisation				X								
Peek package (community screening, automatic reminder short text messaging)					X	X	X					
Standard care				X								
Triage treatment camp								X				
Peek referral reminders to attend Kitale Eye Unit (automatic reminder short text messaging)								X	X	X	X	X
Assessment												
Attendance (uptake) of referrals								X	X	X	X	X

### Participants, interventions and outcomes

#### Study setting

The trial will be conducted in community units that are served by government-run dispensaries and health centres in Trans Nzoia County in northern Kenya. Trans Nzoia County has a population of 818,757 people (2009 census) of which 407,172 (49.7%) were male [44]. It is organised into five sub-counties. There were 173,719 households, with an average of five people per household. The large majority have no Internet access (669,347, 81.8%) [45]. There are 61 government facilities (six hospitals, 12 health centres, 43 dispensaries) and 76 facilities owned privately or by faith-based organisations [46]. Eye services are offered at KEU and through outreach services, provided by eye care staff from KEU to other health facilities. Screening and treatment of eye conditions (triage) is offered during outreach. The trial will be coordinated from Kitale Hospital by a team consisting of a programme manager, administrator, ophthalmic nurses, field workers and an ophthalmologist.

#### Cluster definition

The unit of randomisation for this trial will be Community Units (CU). These are defined as a dispensary or health centre together with the community they serve (Fig. 2). A typical CU comprises a population of 5000–10,000 people. It has a dispensary or health centre, staffed by one or two Community Health Extension Workers (CHEWs). Associated with each CU, there are usually 20–50 CVs [47]. The CHEWs based at the health centre or dispensary train, support and supervise the CVs. To date, 85 CUs have been established and personnel trained in this county [46]. CUs were chosen because it represents the future shape of healthcare in Kenya; they are distributed throughout the county and have a good referral network that provides linkages between community and health system. The CUs with untrained personnel provide a buffer zone that will minimise contamination.

**Fig. 2 Fig2:**
[figure not shown]
Community units, levels of healthcare and referral pathway (prepared by [name])

#### Cluster eligibility criteria

A list of all health facilities with their geo-coordinates as well as corresponding CUs and catchment population will be obtained from the Trans Nzoia County Department of Health. The location of each hospital will be determined using Google Maps. Health facilities without CUs, those with existing screening programs and the communities directly served by KEU will be excluded. We will also exclude all the non-government health facility-associated CUs. From the remaining 66 CUs, a total of 36 CUs will be randomly selected for the study. A restricted cluster random sampling technique (described below) will be applied to allocate the selected CUs to the Peek intervention (18 CUs) or the standard care group (18 CUs). The restriction will be based on the distance and location of the CU’s heath facility relative to KEU.

#### Participant eligibility criteria

All people who consent to participate and present in the community unit area during the study period will be included. People who are unwilling to give consent or who have had an eye condition treated at hospital within two weeks before the beginning of the study will be excluded.

#### Interventions

A comparison of the two arms is shown in Table 2 and Fig. 1. Before the beginning of the trial, households in each of the clusters in both arms will be visited by the field team to explain the study, obtain consent (see Additional file 2) and enumerate the residents. Parents/guardians will provide consent for children. At the beginning of the trial, in both arms, there will be posters and verbal notices (churches and schools) advertising the forthcoming outreach clinic for eye checks, encouraging people with eye problems to self-report to the clinic on a specific date when the team will visit.

**Table 2 Tab2:** Comparison of the interventions in the two arms of the trial

	Intervention arm	Control arm
Consent and enumeration	Yes	Yes
Community sensitisation	Posters and announcement in churches and schools	Posters and announcement in churches and schools
Community screening	Vision assessed at household level using Peek E- acuity by field worker	No vision assessment at household level
	Screening decision using Peek Screening App	No screening
	Personalised text and weekly reminder messages for participants/carers in the relevant local language to attend appointments	No text message
Referral from community to PHC (triage centre)	Self-referring participants and referrals by CV using Peek system?	Self-referring participants
	Automatic referral through Peek system	No referrals
Provision of triage	Trained team composed of ophthalmic clinical officer, ophthalmic nurses and two field workers	Trained team composed of ophthalmic clinical officer, ophthalmic nurses and two field workers
Referral from triage centre to secondary care	Paper referral	Paper referral
	Automatic referral through Peek system and weekly reminder SMS	
Assessment of primary outcome	Same for both arms (trained field worker)	Same for both arms (trained field worker)
Assessment of referrals	Ophthalmic clinical officer	Ophthalmic clinical officer

##### Peek CEH intervention arm

In each cluster, a small mobile team of a ‘Peek User’ (CVs trained specifically on how to use the Peek Community Screening App and who travel to multiple communities to perform their duties) and local CV will visit each household. The CV, a person from that same community, will guide the Peek User around the village. After reconfirming consent, people who are resident in the household at the time of the visit will have a vision assessment. The visual acuity of each eye will be measured separately using the Peek Acuity App [38]. This smartphone application presents a series of E-optotypes in one of four orientations, selected at random. The test algorithm prompts the following screening questions to the parents or guardian with a child (‘*Does the child have any problem with their eyes today?*’) or directly to participant themselves (‘*Do you have any discomfort or pain in your eyes today?*’ and ‘*Do you have a problem with your sight when seeing far or near objects?*’)*.* If the participant is aged ≥ 6 years, the App prompts for distant visuals acuity assessment using Peek Acuity App and assessment of near visual acuity for all people aged ≥ 40 years. Near vision will be assessed at 40 cm using the RADNER reading chart [48]. They will be referred to the PHC for subsequent assessment by the visiting time if: the visual acuity is < 6/12 in either eye; there is any self-reported eye pain or discomfort; there is difficulty seeing distant or near objects; or they are not able see N8 on near vision assessment. Household members absent during the first visit will be asked to join the examination team at the next household or next day.

Those who have reduced visual acuity on screening or report an eye problem will be referred to a health post for triage on a specific date when the KEU team visit. The system will generate several SMS text messages: (1) to the patient and family associate asking them to present to the health facility on a specific day (set to be within four weeks); (2) the CV will receive an SMS list of patients from their community that have been referred; and (3) the CHEW responsible for that CU will similarly receive the same list of referred patients. A weekly reminder SMS will be sent to the patient for them to attend their referral appointment with the last reminder being one day before the appointment.

On the pre-advertised date, a team from KEU will be based at the CU’s dispensary. The participants referred from the household screening because of reduced vision or a specific eye problem will be reminded to attend. They will assess the presenting patients using the current standard procedure (Snellen chart visual acuity, magnifying loop, refraction and direct ophthalmoscopy when indicated). They will provide simple treatments or refer patients to KEU for further assessment as indicated. A pre-numbered paper referral letter will be given to the patient to present at KEU. The referral slip has their study number, name and triage centre, and telephone number, and indicates that assessment and treatment will be provided at no cost. It is expected that they will report to KEU within four weeks from being referred.

Immediately after referral from the PHC, an SMS will be sent to the patient and the family associate asking them to present to KEU. A weekly reminder SMS will be sent for those who have not attended their referral to KEU. An SMS with a list of patients who have not attended their referral will be sent to the CHEW responsible for the PHC.

##### Standard of care (control) arm

In the control arm, there will be no active Peek screening in the community; however, potential participants with eye problems at the community will be notified through community sensitisation (posters and local announcements) that if they have an eye problem to present themselves to the health facility for the triage clinic on a specified date. On that advertised date, the team from KEU will conduct an outreach clinic within the CU, which will be identical to the ones in the Peek arm described above. If an individual needs to be referred to KEU, they will be given an identical referral letter to the ones used in the Peek arm. Each letter will have a unique code number to link the patient referral record to their KEU attendance.

#### Outcomes

##### Primary outcome

The primary outcome is the number of people per 10,000 population (rate) attending triage at a local health facility (PHC) with any confirmed eye conditions (true positives) following a CV referral or by self-referral, within four weeks from the time of sensitisation. The rate will be based on baseline enumeration census for each CU. The true positives will be determined at triage by the hospital outreach team.

##### Secondary outcomes

The secondary otucomes are: (1) the number of people per 10,000 (rate) attending the triage post without any eye condition (false positives) as determined by the eye team; (2) the number of people per 10,000 population (rate) attending KEU within four weeks after being referred from PHC; (3) the proportion of participants referred from the PHC who attend the referral at KEU within four weeks of being referred from a PHC; and (4) the time taken by a participant referred from PHC to attend KEU.

#### Sample size

The sample size of 36 clusters was determined using the Hayes formula for rates in unmatched cluster randomised trials [49]. In Trans Nzoia County, a typical health facility has a catchment population of 5000 people [46]. During previous community outreaches to these health facilities, about 50–100 new patients attended. This translates to an average rate of 15 per 1000 population [50]. Assuming an intraclass correlation coefficient of 0.001, desired power of 90% and significance level of 5%, a sample of 36 CUs (18 in each arm) would be sufficient to detect a difference of 0.5%, from 1.5% in the control arm to 2.0% in the intervention arm (a 33% relative change) in overall attendance rates.

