## Discussion

This trial is designed to evaluate whether the Peek Screening system in the community increases access to eye services at PHC within four weeks for patients with eye problems, as well as to assess whether the same system increases uptake of referrals of people identified with eye problems from PHC to secondary care within four weeks.

One identified limitation of the study would be the number of people who will be screened and referred but have no eye problems (false positives) and may potentially overload the health system. Through the trial, we shall analyse the potential limitations with a view of understanding and providing potential solutions in the future.

The WHO and International Agency for Prevention of Blindeness (IAPB) have set a target of eliminating avoidable blindness by 2020 through early identification and treatement. This study aims to evaluate a system to reduce the prevalence of people with VI through early identification and referral from the community for those with ophthalmic ailments. The system will potentially increase access and uptake of eye services through screening and referral by CVs, for those with eye problems. Through the system, we shall be able to track the process of screening and referral of patients with a view of identifying gaps in the health system and advise policy makers on potential solutions. The results will therefore be relevant and contribute towards realising this goal.

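### The 90% power is stated for overall attendance, whereas the primary test counts only attenders with a confirmed eye condition, so power for the primary test is not established

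*Protocol article*

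**What the plan says.** The Sample size section takes its control rate from outreach history: "During previous community outreaches to these health facilities, about 50–100 new patients attended". Set against the statement that "a typical health facility has a catchment population of 5000 people", this is 10 to 20 per 1000, and the section uses 15 per 1000. It continues: "Assuming an intraclass correlation coefficient of 0.001", with a "desired power of 90% and significance level of 5" per cent, "a sample of 36 CUs (18 in each arm) would be sufficient to detect a difference of 0.5" percentage points, namely "from 1.5% in the control arm to 2.0% in the intervention arm (a 33% relative change) in overall attendance rates".

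The Primary outcome section defines something narrower, the rate of people "attending triage at a local health facility (PHC) with any confirmed eye conditions (true positives"). The section on analysis of the primary outcome uses the same numerator: attenders with a confirmed condition, divided by the enumerated cluster population, compared between arms by a t-test on cluster-level rates. Attenders found to have no eye condition are the first secondary outcome, with their own analysis. The Discussion names as a limitation "the number of people who will be screened and referred but have no eye problems (false positives").

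**The concern.** The power claim is tied by name to a quantity other than the one the primary test compares. Overall attendance is the sum of the primary outcome and the first secondary outcome, so the two rates coincide only if nobody attends without an eye condition. The protocol does not assume that, because it plans to count and analyse such attenders. It gives no share of attenders expected to be confirmed and no confirmed-case rate for either arm. Nor does it say that attendance stands in for the primary outcome.

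This is not a detail left to an analysis plan. The article makes a specific power claim, and that claim does not match its own outcome definition. Readers will use the 90% to judge whether the trial could have detected a worthwhile effect, particularly if the primary result is null.

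**Working it through.** **Inputs stated in the Sample size section.** Rates p0 = 0.015 and p1 = 0.020; cluster size m = 5000; intraclass correlation (ICC) 0.001; c = 18 CUs per arm; significance level 5%. The section does not give sidedness; two-sided is used here and reproduces the figure.

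**Step 1: reproduce the stated figure.** The unmatched-cluster formula is

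c = 1 + (1.960 + 1.282)² × [p0(1 − p0) + p1(1 − p1)] × (1/m + ICC) / (p1 − p0)²

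- (1.960 + 1.282)² = 10.51
- p0(1 − p0) + p1(1 − p1) = 0.014775 + 0.019600 = 0.034375
- 1/m + ICC = 0.0002 + 0.001 = 0.0012
- c = 1 + 10.51 × 0.034375 × 0.0012 / 0.000025 = 18.3

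Power of a two-sample t-test with 34 degrees of freedom:

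- Design effect = 1 + 4999 × 0.001 = 5.999
- SE = √(0.034375 × 5.999 / 5000 / 18) = 0.001514
- Non-centrality = 0.005 / 0.001514 = 3.30
- Power = 89.4%

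The stated 18 per arm and 90% are therefore right for overall attendance.

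**Step 2: apply the same calculation to confirmed cases.** The documents give no confirmed share, so every share below is an assumption. Confirmed rates are 0.015 × control share and 0.020 × Peek share, except in case C, where the Peek rate is the control rate plus 0.005.

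| Case | Share, control / Peek | Confirmed rates | Power |
|---|---|---|---|
| A. Common share, 33% relative effect kept | 0.95 / 0.95 | 1.425% vs 1.90% | 87.8% |
| A | 0.90 / 0.90 | 1.35% vs 1.80% | 86.0% |
| A | 0.80 / 0.80 | 1.20% vs 1.60% | 81.7% |
| A | 0.70 / 0.70 | 1.05% vs 1.40% | 76.3% |
| A | 0.60 / 0.60 | 0.90% vs 1.20% | 69.7% |
| B. Lower share under Peek | 0.95 / 0.90 | 1.425% vs 1.80% | 71% |
| B | 0.90 / 0.80 | 1.35% vs 1.60% | 42% |
| C. Full 0.5 points in confirmed cases | 0.90 control | 1.35% vs 1.85% | 91.8% |
| C | 0.80 control | 1.20% vs 1.70% | 94.1% |

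Worked example, 0.90 / 0.80: variance sum 0.0135 × 0.9865 + 0.0160 × 0.9840 = 0.029062; SE = √(0.029062 × 5.999 / 5000 / 18) = 0.001392; non-centrality = 0.0025 / 0.001392 = 1.80; power 42%.

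**Step 3: what the cases imply.** Overall attendance rises by 5 per 1000. In case B, confirmed cases make up 3.75 of those 5 (75%) at 0.95 / 0.90, and 2.5 of 5 (50%) at 0.90 / 0.80. In case C they make up all 5.

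**Step 4: sensitivity to how clustering is carried over.** The table holds the ICC at 0.001 as the rate falls. If instead the between-cluster coefficient of variation is fixed at √(0.001 × 0.985 / 0.015) = 0.256, power for 1.5% vs 2.0% is 84.5%. With a common share it then falls only to 84.0% at 0.90 and 81.1% at 0.60. The constant-ICC form is the one that reproduces 18 per arm. The loss in case A therefore depends partly on that choice; at 0.90 / 0.80 in case B it does not (42% either way).

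**The case against.** The strongest reply is that little may be lost. Control attenders present themselves because they believe they have an eye problem, and any confirmed condition counts, so the confirmed share could be close to 1. At 0.95 in both arms power is 88%, a trivial change. The target is also stated as an absolute difference, and the primary analysis estimates a rate difference. If the 0.5 points are all confirmed cases on a lower base, power rises. Peek referral requires reduced acuity, failed near vision or a reported problem, and the Rationale says volunteers could make referral decisions accurately. Finally, the primary result will carry a 95% confidence interval, so a null finding need not be read from planned power.

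Most of this stands, and it rules out three stronger readings that a reader might infer:

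- **That the sample-size arithmetic is wrong.** It is not; it reproduces for its own endpoint.
- **That the control rate for the primary outcome must be below 1.5%.** This follows only if some past attenders had no eye condition, and the article does not say whether they did.
- **That the trial is underpowered because Peek will bring in more people without eye problems.** The Discussion raises false positives as a possible burden, but gives no rate and does not say that the confirmed share will be lower than under standard care. The objective of more appropriate use of services points, if anything, the other way.

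The reply does not remove the mismatch. Nothing in the article says that the confirmed-case rates are 1.5% and 2.0%, or that all attenders may be treated as confirmed.

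**Conclusion.** The point holds as a mismatch between the endpoint used for sizing and the endpoint tested. Power for the primary test is unsupported; it is not shown to be low. With 18 CUs per arm, clusters of 5000, ICC 0.001 and a two-sided 5% t-test, the cases tabulated run from 42% to 94%, against 89.4% for overall attendance. The spread comes from assumed confirmed shares and from whether the planned effect is read as a relative change or as an absolute difference in confirmed cases. The article settles neither. The less favourable end needs a confirmed share ten points lower under Peek than under standard care, for which the article gives no evidence. The 90% should therefore not be quoted for the primary outcome as the text stands, nor should any of the lower figures be quoted as the trial's true power.

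**What to change.** Keep 36 CUs, the outcome and the analysis. Rewrite the sample-size paragraph to:

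1. say that the 90% (89.4% on recalculation) applies to overall attendance of 1.5% vs 2.0%;
2. state the expected confirmed-case rate in each arm, with its source, and the resulting power for the primary outcome;
3. add a short sensitivity table covering less and more favourable cases, including a lower confirmed share under Peek and the case where the full 0.5 points are confirmed cases.

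If past outreach records hold diagnoses, they would be the natural source for the control share; the article does not say whether they do. The alternative to items 2 and 3 is a reasoned statement of why all attenders can be treated as confirmed.

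The cost is one paragraph and no added clusters. The downside is that the stated power may become less favourable. Recruitment was already under way when the article was submitted, so any assumed rates should come from sources outside the trial's own outcome data.
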